### Treatment plan

Upon registration, which occurs after completing a minimum of 16 weeks or a maximum of 26 weeks of first-line systemic therapy, patients will be randomized to one of two treatment arms. Patients in arm 1 will undergo TAT followed by SOC chemotherapy per institutional practice. For patients in arm 1, the overall treatment plan will be discussed in a multidisciplinary setting, and the patient will be evaluated by physicians from all planned treatment modalities as early as possible for treatment planning. TAT will consist of surgical resection, MWA, and/or SABR to all sites of disease and must be completed within 90 days from randomization. At least one measurable site of metastatic disease needs to be present after completion of induction systemic therapy for treatment, and patients with a complete response to systemic therapy at time of randomization will be removed from the trial. At least one metastatic site must be treated with SABR. The remaining sites can be treated by either SABR with or without surgery and/or MWA. For treatment with SABR, the goal is to deliver a radiation dose that maximizes local control at the treatment site within the confines of anatomic and normal tissue constraints. However, sites must be credentialed for the treatment modality that they intend to use on all patients. All radiation therapy plans will be reviewed in real-time for quality assurance.

Resection of each planned metastatic lesion will be approached with the intent of an R0 resection. If surgical resection of a given metastasis is incomplete with gross or microscopic residual margins, the treatment team should strongly consider using an alternative ablative treatment modality such as MWA or SABR to any residual gross or microscopic disease. When addressing liver metastases, non-anatomic resection will be considered when feasible, and MWA will be considered to allow for a parenchymal-sparing approach for deep lesions less than 3 cm in size. For all patients who undergo surgery during protocol treatment, the preoperative imaging, operative note, surgical pathology report, and adverse events with 30 days of surgery will be reviewed by the study team for quality assurance.

MWA can be delivered either intra-operatively or using a percutaneous approach. Multiple electrodes and overlapping ablations will be permitted to ensure adequate coverage of the target. A minimum margin of 5.0 mm will be required for lesions treated with MWA on this study. Initial assessment of the ablation zone will be verified immediately intra-procedurally using ultrasound, computed tomography (CT), or magnetic resonance imaging (MRI). If a margin of < 5.0 mm is observed at initial assessment, additional ablation will be attempted to extend the ablation zone, expand the area of insufficient coverage and provide for at least 5.0 mm minimal margin around the target tumor. If at the first imaging timepoint the tumor is deemed to be incompletely covered, the tumor can undergo repeat treatment without penalization. As quality assurance, the study team will review pre-treatment imaging, the procedure notes, and adverse events within 30 days of treatment associated with MWA. Imaging from the first assessment timepoint at 14–18 weeks post-randomization will also be reviewed to ensure completion of planned ablation.

Lesions that are too small to be treated with any of the modalities included in TAT will be monitored and treated if they progress to a size that is amenable to treatment, and they will not be considered as Response Evaluation Criteria in Solid Tumors (RECIST) progression. Following completion of TAT, the treating healthcare team will consider re-starting systemic therapy within 2 weeks if no surgery is performed or within 4 weeks if surgery is included as part of TAT. Use of maintenance systemic therapy or systemic therapy breaks is permitted at the discretion of the treatment team. Patients randomized to arm 1 with the primary tumor intact will have the primary tumor removed within 6 months of randomization. Resection of the primary tumor may be performed at the same time as metastasectomy or may be staged per discretion of the healthcare team. For patients with primary rectal cancers, the use of pre-operative radiation or chemoradiation will be left to the discretion of the healthcare team.

Patients randomized to arm 2 will continue with systemic therapy with use of maintenance chemotherapy per institutional practice. Local metastatic-directed therapy will not be permitted except for palliation as per institutional standard practices. Palliative radiation therapy will be permitted for lesions causing symptoms that are not controlled by medical therapy with acceptable regimens including 30 Gy in 10 fractions, 24 Gy in 6 fractions, 20 Gy in 5 fractions, 8 Gy in 1 fraction, or an equivalent regimen. Systemic therapy breaks are permitted at any time at the discretion of the treatment team.

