** For patients on Arm 1, physical examination, vitals, adverse event (AE) assessment, and labs are required at 14–18 weeks post-randomization. For patients on Arm 2, physical examination, vitals, AE assessment and labs are required at least prior to the start of each cycle for patients receiving active systemic therapy and 14–18 weeks post-randomization. For patients on a treatment break, physical examination, vitals, AE assessment and labs are required at 14–18 weeks post-randomization

*** Following the first assessment timepoint at 14–18 weeks post-randomization, patients should undergo physical examination, AE assessment, labs, and staging scans every 3 months (+/- 1 month) until disease progression or start of off-protocol anticancer therapy, whichever comes first. Off-protocol anticancer therapy incudes any experimental agent, a systemic therapy regimen not specifically included outlined in the protocol, or, for patients randomized to Arm 2 (institutional SOC therapy), local metastatic-directed therapy other than what is delivered for palliation. Patients who discontinue study treatment due to disease progression (or who start a new anticancer therapy after discontinuing study treatment for reasons other than disease progression) should be followed every 6 months for survival until 5 years after registration

1 Solicited adverse events are to be collected starting prior to treatment until off-treatment. Routine adverse events are to be collected starting after registration until the end of survival follow-up. For patients who register before/during systemic therapy, the first routine adverse event assessment should take place after registration but prior to Day 1 of the next planned cycle of systemic therapy

2 Albumin, alkaline phosphatase, total bilirubin, bicarbonate (or total CO2), BUN, chloride, creatinine, glucose, potassium, total protein, SGOT (AST), SGPT (ALT), and sodium

3 For women of childbearing potential. Must be done ≤ 14 days prior to registration

4 Perform at baseline (prior to initiation of systemic therapy, if applicable), ≤ 28 days prior to registration, ≤ 28 days prior to randomization, 14–18 weeks post-randomization, then every 3 months (+/- 1 month) for the first three years after randomization, then every 6 months (+/- 1 month) for years 4–5 after registration. Any measurements of biochemical response should occur in conjunction with the radiologic assessments for disease status

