### Assessment and follow-up

Radiologic response will be evaluated using the RECIST version 1.1 guidelines [27]. A local recurrence will be defined differently based on the modality of treatment. For patients treated with SABR, a recurrence will be deemed local if located in or directly adjacent to the planning target volume. For a site treated using MWA, a recurrence will be deemed local if it is within 1 cm of the treatment site. For patients who undergo surgery, a recurrence will be considered local if it is located at the margin of resection.

Adverse events (AEs) will be graded using the Common Terminology Criteria for Adverse Events (CTCAE) Version 5.0. Solicited AEs will be collected at baseline prior to treatment until off treatment. Routine AEs will be collected starting after registration until the end of survival follow-up. The first treatment response assessment timepoint will be at 14–18 weeks post-randomization, and then every 3 months until disease progression or at the start of off-protocol anticancer therapy. Off-protocol anticancer therapies consists of any investigational agent, systemic therapy regimen(s) not included in the protocol; for patients randomized to arm 2, this includes any local metastatic-directed therapy other than therapy delivered with palliative intent. All visits will include a history and physical examination, laboratory studies, AE assessment, and imaging with CT of the chest along with CT or MRI of the abdomen and pelvis or, alternatively, a positron emission tomography/computed tomography (PET/CT). All patients, irrespective of whether continuing on study, or who are receiving off protocol therapy, will be followed for OS (except patients who withdraw consent).

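### Growth of lesions too small for TAT is exempted from RECIST progression in the arm 1 text only; if event-free survival counts RECIST progression, its event rule differs by arm and tends to favour TAT

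*Protocol article*

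**What the plan says.** **Arm 1 (Treatment plan).** Lesions too small for any TAT modality "will be monitored and treated if they progress to a size that is amenable to treatment, and they will not be considered as" RECIST progression. The microwave ablation text adds that, if a tumor proves incompletely covered at the first imaging timepoint, "the tumor can undergo repeat treatment without penalization".

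**Arm 2 (Treatment plan).** "Local metastatic-directed therapy will not be permitted except for palliation as per institutional standard practices". Nothing is said about growth of very small lesions.

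**Both arms (Assessment and follow-up).** "Radiologic response will be evaluated using the RECIST version 1.1 guidelines"; no arm is named.

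**Off-protocol therapy.** Investigational agents and systemic regimens outside the protocol count in either arm. In addition, "for patients randomized to arm 2, this includes any local metastatic-directed therapy other than therapy delivered with palliative intent". The follow-up footnote to Table 2 agrees: "for patients randomized to Arm 2 (institutional SOC therapy), local metastatic-directed therapy other than what is delivered for palliation".

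**End of scheduled assessment.** Assessment and follow-up has it run "every 3 months until disease progression or at the start of off-protocol anticancer therapy". The Table 2 follow-up footnote has "until disease progression or start of off-protocol anticancer therapy, whichever comes first". Footnote B of the same table has imaging continue until progression or relapse and mentions no stop at off-protocol therapy.

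**Endpoints.** Overall survival (OS) is primary and is followed in all patients except those who withdraw consent. Event-free survival is secondary; the article does not list its events or censoring rules.

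**The concern.** The small-lesion sentence classifies an outcome, yet it stands inside one arm's treatment text. Its trigger is that TAT modalities cannot treat the lesion, and its consequence is later local treatment. Neither fits arm 2, where local treatment is barred except for palliation. Read as written, growth of such a lesion is exempt in arm 1 and has no stated exemption in arm 2.

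Ascertainment may differ too. Treating the grown lesion is protocol therapy in arm 1, so scheduled assessment goes on. In arm 2 the same act, without palliative intent, is off-protocol therapy, and under two of the three passages on assessment it ends the schedule.

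Treating teams know the allocation, and the article gives no size limit for a lesion that is too small. If event-free survival counts RECIST progression, part of an apparent benefit could come from the counting rule rather than from TAT.

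**Working it through.** **1. The plan's own figure.** There is none for event-free survival. The OS figure is 208 events (hazard ratio 0.7, 80% power, one-sided 0.05, futility looks at 25% and 50%, rho = 1.5).

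- Fixed design: 4 × (1.645 + 0.842)² / (ln 0.7)² = 4 × 6.185 / 0.1272 ≈ 194.5, so 195 events.
- With non-binding futility and beta spending 0.2 × t^1.5, the required drift is 2.570: 4 × 2.570² / 0.1272 ≈ 207.7, so 208 events.

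The stated 208 reproduces. It rests on deaths only, so no progression rule can change it.

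**2. The texts side by side.**

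| Situation | Arm 1 | Arm 2 |
|---|---|---|
| Growth of a lesion too small for TAT | stated not to be RECIST progression | no exemption stated; general RECIST 1.1 sentence |
| Non-palliative local treatment of it | protocol therapy | off-protocol therapy |
| Scheduled assessment afterwards | continues | stops (Assessment and follow-up; Table 2 follow-up footnote) or continues to progression or relapse (footnote B) |

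**3. Illustration of direction and size.** From the documents: 173 patients per arm, a 60-month cut-off (the minimum follow-up) and a one-sided 5% log-rank test (borrowed from the OS design). Assumed: exponential times, a median event-free survival of 8 or 12 months, no true difference, and a share q of first events exempted in arm 1 only. Each cell has 2,000 runs. The paired values are for medians of 8 and 12 months.

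| q | Counted 6 months late: HR | False positives | Replaced by next event: HR | False positives |
|---|---|---|---|---|
| 0 | 1.00, 1.00 | 4.7%, 4.6% | 1.00, 1.00 | 5.2%, 6.0% |
| 5% | 0.97, 0.98 | 10.2%, 7.0% | 0.95, 0.95 | 11.2%, 11.6% |
| 10% | 0.95, 0.96 | 11.6%, 10.5% | 0.91, 0.91 | 22.4%, 22.7% |

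The simulation error (one standard error) is √(0.05 × 0.95 / 2000) ≈ 0.5 points near 5% and √(0.22 × 0.78 / 2000) ≈ 0.9 points near 22%. The 10.2% cell is probably high by chance: a longer run of the same simulation put it nearer 8% and left the overall ranges of about 7% to 12% and 11% to 22% in place.

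**4. Cross-check by formula.** If exemption cuts the arm 1 hazard permanently by q, the false-positive rate is 1 − Φ(1.645 + ln(1 − q) × √(D/4)), with D events.

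- D = 300 (assumed), q = 5%: 1.645 − 0.0513 × 8.660 = 1.201, giving 0.115.
- D = 300, q = 10%: 1.645 − 0.1054 × 8.660 = 0.733, giving 0.232.
- D = 250 (assumed): 0.108 and 0.208.

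This matches the replaced-by-next-event case. It is the harsher model, and the 6-month delay is the milder one.

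**The case against.** The strongest reply is that the article never defines the events or censoring of event-free survival, and an article may leave both to the full protocol. That document might already treat the two arms alike. This stands: the bias is conditional. What remains is the one-arm rule that the article does state.

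The lack of an exemption in arm 2 is inferred from silence. Whether growth of a very small lesion would be progression at all depends on RECIST 1.1, which is cited but not shown. This also stands in part, although a rule triggered by unsuitability for TAT and ending in local treatment does not carry over naturally to arm 2.

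A reader might take the repeat-ablation clause as a second case of forgiven progression. The text does not support that. Its trigger is incomplete coverage, the same imaging is reviewed to confirm that the planned ablation was completed, and no endpoint is named.

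A reader might also infer informative censoring, mainly in arm 2. The documents do not say that event-free survival is censored at off-protocol therapy, give no frequency of such therapy, and contain footnote B, which has no such stop. The systemic-therapy triggers apply in both arms.

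Finally, the affected group may be small. Eligibility requires metastatic lesions amenable to TAT, and only patients whose sole first progression is in a too-small lesion are affected.

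**Conclusion.** The point holds in conditional form. As written, the handling of growth in too-small lesions is specific to arm 1, and so is the status of non-palliative local therapy. If event-free survival counts RECIST progression, the comparison tends to favour TAT without any true effect.

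The direction is clear; the size is not. With assumed shares of 5% to 10%, the false-positive rate is about 7% to 12% if exempted events are only 6 months late, and about 11% to 22% if they are replaced by the next event. The shares, medians and event counts are all assumptions. A share below 5% would bring the rate closer to the nominal 5%.

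The flat statement that event-free survival is biased goes further than the article allows. Primary OS, its 208 events and its power are untouched. This should be corrected because a secondary between-arm result could otherwise be hard to interpret; it does not threaten the trial's main conclusion.

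**What to change.** - State for event-free survival one progression rule for initially too-small lesions in both arms. Primary version: growth that meets RECIST 1.1 progression is an event on its scan date in either arm, whether or not the lesion is then treated.
- Add a sensitivity analysis that exempts such growth in both arms. It needs the too-small lesions recorded on the same terms in both arms, best done before randomization.
- Reconcile Assessment and follow-up and the Table 2 follow-up footnote (assessment ends at off-protocol therapy) with footnote B (imaging until progression or relapse).
- Collect the dates and results of routine scans until progression in both arms, also after off-protocol therapy.
- If the full protocol already does this, a clarifying clause at the small-lesion sentence is enough.

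The cost is endpoint wording and some extra data collection from routine scans. The downside is a slightly less favourable event-free survival in arm 1. Clinical management, including the option to treat a grown lesion or repeat an ablation, does not change.

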### Assessment and follow-up

Radiologic response will be evaluated using the RECIST version 1.1 guidelines [27]. A local recurrence will be defined differently based on the modality of treatment. For patients treated with SABR, a recurrence will be deemed local if located in or directly adjacent to the planning target volume. For a site treated using MWA, a recurrence will be deemed local if it is within 1 cm of the treatment site. For patients who undergo surgery, a recurrence will be considered local if it is located at the margin of resection.

Adverse events (AEs) will be graded using the Common Terminology Criteria for Adverse Events (CTCAE) Version 5.0. Solicited AEs will be collected at baseline prior to treatment until off treatment. Routine AEs will be collected starting after registration until the end of survival follow-up. The first treatment response assessment timepoint will be at 14–18 weeks post-randomization, and then every 3 months until disease progression or at the start of off-protocol anticancer therapy. Off-protocol anticancer therapies consists of any investigational agent, systemic therapy regimen(s) not included in the protocol; for patients randomized to arm 2, this includes any local metastatic-directed therapy other than therapy delivered with palliative intent. All visits will include a history and physical examination, laboratory studies, AE assessment, and imaging with CT of the chest along with CT or MRI of the abdomen and pelvis or, alternatively, a positron emission tomography/computed tomography (PET/CT). All patients, irrespective of whether continuing on study, or who are receiving off protocol therapy, will be followed for OS (except patients who withdraw consent).

### Correlative studies

Patients may elect to consent to collection of blood and archival formalin-fixed paraffin-embedded tissue for future genomic analyses. Three 10 mL blood samples will be collected at several time points including within 14 days of pre-registration for those who enroll prior to initiating systemic therapy, at randomization, at 4 months, 8 months, and 1 year after randomization, and at disease progression.

### Statistics

#### Sample size

Per study design, a total of 346 patients (173 per arm) are needed to evaluate the primary endpoint. An additional 18 patients (5% inflation) will be accrued to allow for withdrawal after randomization and major violations. Thus, the total planned target accrual will be 364 patients. Approximately 405 patients will be pre-registered to reach this target accrual, allowing for a 10% drop out during the initial 16 to 26 weeks of SOC systemic therapy due to complete response status, progressive disease, unacceptable toxicity, patient withdrawing consent, treating physician’s decision, etc. With an anticipated accrual of 6.5 patients per month, we estimate the accrual period to be 4.7 years.

### Power analysis

Eligible patients will be stratified by the number of metastatic organ sites (1–2 vs. 3–4), timing of metastatic disease diagnosis (synchronous metastatic disease vs. metachronous metastatic disease diagnosed ≥ 12 months following completion of definitive treatment for initial diagnosis), and presence of at least one metastatic site outside the liver and lungs (yes vs. no). Participants will be assigned to one of two treatment arms in a 1:1 ratio, using a dynamic allocation algorithm [28]. This study will utilize a group sequential design with two interim analyses for futility after observing 25% (52 events) and 50% (104 events) of events, adopting the Rho family (Rho = 1.5) beta spending function for controlling the type II error rate. Based on historical data, the median OS is assumed to be 26 months (following 16–26 weeks of initial SOC systemic therapy) for newly diagnosed mCRC patients treated with SOC systemic therapy. We assume an accrual rate of 6.5 patients per month, minimum follow-up on all patients of 60 months, exponential survival, and a one-sided log-rank test for superiority conducted at a one-sided significance level of 0.05. Based on these assumptions, a total number of 208 events will provide 80% power to detect an HR of 0.7 at a one-sided significance level of 0.05 requiring randomization of at least 346 evaluable patients (173 per arm).

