**Methods:**

The Evaluating Radiation, Ablation, and Surgery (ERASur) A022101/NRG-GI009 trial is a randomized, National Cancer Institute-sponsored phase III study evaluating if the addition of metastatic-directed therapy to standard of care systemic therapy improves OS in patients with newly diagnosed limited mCRC. Eligible patients require a pathologic diagnosis of CRC, have *BRAF* wild-type and microsatellite stable disease, and have 4 or fewer sites of metastatic disease identified on baseline imaging. Liver-only metastatic disease is not permitted. All metastatic lesions must be amenable to total ablative therapy (TAT), which includes surgical resection, microwave ablation, and/or stereotactic ablative body radiotherapy (SABR) with SABR required for at least one lesion. Patients without overt disease progression after 16–26 weeks of first-line systemic therapy will be randomized 1:1 to continuation of systemic therapy with or without TAT. The trial activated through the Cancer Trials Support Unit on January 10, 2023. The primary endpoint is OS. Secondary endpoints include event-free survival, adverse events profile, and time to local recurrence with exploratory biomarker analyses. This study requires a total of 346 evaluable patients to provide 80% power with a one-sided alpha of 0.05 to detect an improvement in OS from a median of 26 months in the control arm to 37 months in the experimental arm with a hazard ratio of 0.7. The trial uses a group sequential design with two interim analyses for futility.

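### The 60-month minimum follow-up in the power section does not fit the 346 patients and 208 deaths said to follow from it

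*Protocol article*

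**What the plan says.** The Power analysis section gives the design inputs in one sentence: "We assume an accrual rate of 6.5 patients per month, minimum follow-up on all patients of 60 months, exponential survival", together with "a one-sided log-rank test for superiority conducted at a one-sided significance level of 0.05". Just before it, "the median OS is assumed to be 26 months" for the control arm, and the abstract describes the target improvement as "from a median of 26 months in the control arm to 37 months in the experimental arm". The section then presents its result as following from these assumptions: "a total number of 208 events will provide 80% power to detect an HR of 0.7 at a one-sided significance level of 0.05", with a requirement of at least 346 evaluable patients, 173 per arm.

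Two futility looks are set at 52 and 104 deaths, called 25% and 50% of events, with rho-family beta spending (rho = 1.5). The Sample size section adds 18 patients (5%) on top of 346 for withdrawals and major violations, giving 364. No loss-to-follow-up rate enters the event calculation.

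A footnote to Table 2 says that patients who stop study treatment for progression, or who start another anticancer therapy, "should be followed every 6 months for survival until 5 years after registration". The Assessment and follow-up section says that all patients are followed for overall survival unless they withdraw consent, and gives no end date there.

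**The concern.** When accrual rate, minimum follow-up, survival model and medians are all fixed, the expected number of deaths for a given sample size is determined. Sixty months is more than twice the control median and well beyond the experimental median, so most patients would have died by then. A target of 208 deaths is only 60% of 346 (208/346 = 0.60), which looks too low for that much follow-up.

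At stake are the stated origin of the sample size and the expected date of the trial's only efficacy test. A minimum follow-up on all patients is usually understood to fix when the final analysis happens. If the number is not the one used, nobody planning data-monitoring meetings or data cut-offs can tell from the article when the final analysis is due.

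**Working it through.** **Inputs.** Power analysis section: one-sided alpha 0.05, power 80%, HR 0.7, control median 26 months, 6.5 patients per month, 60 months minimum follow-up, exponential survival, 1:1 allocation, looks at 52 and 104 of 208 deaths, rho = 1.5. Abstract: experimental median 37 months (26/0.7 = 37.1). Assumptions added here: uniform accrual, no loss to follow-up, months counted from the start of accrual.

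**1. Reproduce the 208 deaths.** A fixed design needs 4(1.645 + 0.842)²/(ln 0.7)² ≈ 194.4, so 195 deaths. At 208 deaths without interim looks, power is 82.3%. With non-binding futility looks at 25% and 50%, cumulative beta spent is 0.2 × 0.25^1.5 = 0.025 and 0.2 × 0.5^1.5 = 0.071. The bounds are then Z = −0.674 and 0.259, or observed hazard ratios of about 1.21 and 0.95. With a final critical value of 1.645, power is 80.05% (80.9% if the bounds are binding). So 208 deaths, the looks at 52/208 = 25% and 104/208 = 50%, and 80% power agree with one another.

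**2. Expected deaths from 346 patients at 60 months.** For uniform accrual over A months, minimum follow-up f and hazard λ:

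P(death) = 1 − e^(−λf) × (1 − e^(−λA))/(λA)

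- A = 346/6.5 = 53.2 months
- control λ = ln 2/26 = 0.02666; experimental λ = 0.7 × 0.02666 = 0.01866
- f = 60: P = 0.892 (control) and 0.793 (experimental)
- deaths = 173 × 0.892 + 173 × 0.793 = 154.3 + 137.2 = 291.5

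If both arms had the 26-month median, the figure would be 346 × 0.892 = 308.7.

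**3. The same with every patient censored at exactly 60 months.** 173 × (2 − e^(−60 × 0.02666) − e^(−60 × 0.01866)) = 173 × (0.798 + 0.674) = 254.6 deaths.

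**4. Solve for the value that fits.**

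| Held fixed | Solved for | Result |
|---|---|---|
| 346 patients, 208 deaths | minimum follow-up | 17.2 months, so month 53.2 + 17.2 = 70.4 |
| 364 patients, 208 deaths | minimum follow-up | 12.8 months, so month 56.0 + 12.8 = 68.8 |
| 60 months, 208 deaths | patients | about 253 |
| 346 patients, 60 months, 208 deaths | loss to follow-up | about 14% per year (about 53% by month 60) |

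Sixty months after the 346th patient is month 53.2 + 60 = 113.2, about 43 months later than the expected 208th death.

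**5. What would change if the final analysis did wait for 60 months.** At 291 deaths the looks fall at 52/291 = 18% and 104/291 = 36% of information. Power is about 87% if the futility bounds built for 208 are kept, and about 89% if the beta spending is recomputed for 291.

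**The case against.** The best defence is that the plan is event-driven. The only quantity tied to power is the 208 deaths, both interim looks are fractions of that total, and 60 months appears among the assumptions rather than as a time of analysis. An article may also leave the exact trigger wording to the full protocol. On this reading 60 months is simply the length of survival follow-up, and nothing in the test, alpha, event target or looks is disturbed. All of that stands, and it limits the point to the derivation and the timing.

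Three stronger readings are tempting but unsupported:

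- A reader might infer that the trial cannot reach 208 deaths or is underpowered. The reverse holds: 60 months overshoots 208, and power would rise if the analysis waited.
- A reader might infer two competing triggers, with the timing of the efficacy test open to choice. The article names no follow-up trigger; this would be drawn from an ambiguous assumption.
- A reader might take 60 months as a cap on every patient's survival follow-up. The Table 2 footnote concerns patients who progressed or changed therapy, and the Assessment and follow-up section sets no such limit. The 255-death figure is therefore a sensitivity case and not a documented rule.

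The defence does not rescue the derivation. The article does not leave the follow-up assumption to another document: it states it, calls it a minimum on all patients, and says the sample size results from it. Loss to follow-up does not explain the gap either. None is stated in the event calculation, and the 5% allowance is added on top of 346.

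**Conclusion.** The concern holds as an inconsistency in the sample-size derivation and the analysis timing, at should-fix level. Under the stated accrual, medians and exponential survival, and with no loss to follow-up, 60 months minimum follow-up implies about 291 deaths, some 83 more than the 208 stated (291 − 208). Even the most restrictive per-patient reading gives about 255. The 346 patients fit 208 deaths only with about 17 months of minimum follow-up. That value is back-solved: it shortens to about 13 months if all 364 patients are counted, and it would lengthen with any loss to follow-up. The value actually entered in the design calculation is not visible in the article.

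The event target, the interim information fractions and the 80% power are mutually consistent, and neither power nor type I error control suffers if the final analysis is run at 208 deaths.

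**What to change.** In the Power analysis section:

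1. State that the final overall survival analysis takes place at the 208th death.
2. Replace the 60-month minimum follow-up with the value actually used to derive 346. By this calculation it is about 17 months, with the 208th death expected near month 70, assuming no loss to follow-up. If a loss rate was used, state it.
3. If 60 months is meant as the length of survival follow-up, say so there, and say to which patients it applies so that it agrees with the Table 2 footnote and the Assessment and follow-up section.

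If the final analysis is really meant to wait until every patient has 60 months, restate the expected deaths (about 291), the power (about 87% with the futility bounds unchanged, about 89% with them recomputed) and the information fractions of the looks (about 18% and 36%).

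The cost is one paragraph of wording and a rerun of the design calculation. No patients are added, and if the analysis stays at 208 deaths the futility bounds do not change.
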